### Statistical analysis

The results will be evaluated based on the intention to treat analysis.

The incidence rates will be estimated using Kaplan-Meier survival curves that will be compared using logrank analysis. The treatment efficacy will be assessed by multivariate analyses using Cox's regression model.

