### Primary objective

To assess the effectiveness of screening and treatment of coronary artery disease on the occurrence of cardiac events (acute coronary syndromes or cardiac death) in a group of patients with type 2 diabetes considered at intermediate/high risk according to the risk chart.

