### Secondary objective

We will also consider and analyse the impact of screening and treatment of coronary artery disease on the occurrence of symptomatic heart failure. Actually diabetic patients run a higher risk of developing symptomatic heart failure especially after an acute coronary syndrome [13].

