### Study Design

The aim of the study is to assess whether screening and treatment of asymptomatic coronary artery disease reduces risk of cardiac events and cardiac death. A prospective *open-label *randomized controlled trial comparing a strategy based on exercise testing aimed at revascularization with management based on pharmacological/behavioural treatment of traditional risk factors has been adopted.

Eligible patients will be randomly assigned (ratio 1:1) to undergo exercise tolerance testing or to continue to be followed by our diabetes outpatients services. Best medical/behavioral therapy will be offered to both groups. Those patients with a positive exercise tolerance testing will be studied by coronary angiography and treated according to the severity of coronary lesions by percutaneous stenting or surgery (Figure 1).

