### Participant enrolment

All eligible patients will be asked to participate. Once informed, they will be requested to sign a consent form. At the first visit they will be given a brochure containing detailed information about diabetes, hypertension, atherosclerosis and prevention. All participants will continue with regular follow ups scheduled by the referral diabetes outpatients service.

All smokers will be invited to quit. Physical activity and diet will be encouraged.

At the time of first visit a set of data will be collected:

Personal and clinical data regarding diabetes, cardiovascular risk factors, medications and blood pressure measurements will be collected. Information on laboratory parameters including lipid profile, serum creatinine, HbA1c will also be collected. Cardiovascular risk will be calculated according to the Italian risk chart provided by Istituto Superiore di Sanità [14].

All this data will be abstracted, reported in ad hoc forms and centrally collected.

During follow up the occurrence of any clinical event included in the end-points will be notified and verified through the registers of local Hospital admissions. After the completion of follow each patient will be contacted for the final visit.

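### Kaplan-Meier slightly overstates the incidence of heart failure, because death precludes it; cumulative incidence with deaths shown by arm would be the better report

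*Protocol article*

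**What the plan says.** In the Protocol article, the Statistical analysis section commits to intention to treat and then states: "The incidence rates will be estimated using Kaplan-Meier survival curves that will be compared using logrank analysis". It continues: "The treatment efficacy will be assessed by multivariate analyses using Cox's regression model". It names no endpoint, so the same methods are the only ones stated for both outcomes. It gives no rule for deaths that are not part of an endpoint.

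The Primary objective is a composite of acute coronary syndrome and cardiac death. The Secondary objective is heart failure on its own: "We will also consider and analyse the impact of screening and treatment of coronary artery disease on the occurrence of symptomatic heart failure". The Study Design section says the trial asks whether the strategy "reduces risk of cardiac events and cardiac death".

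On event capture, the Participant enrolment section says that "the occurrence of any clinical event included in the end-points will be notified and verified", using local hospital admission registers, with a final visit after follow-up. Under Interim Analyses, the observed event rate may influence how long patients are followed.

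**The concern.** One minus Kaplan-Meier estimates the proportion who experience an event only if nothing else can make the event impossible. Death makes heart failure impossible. The article does not say that deaths are censored, but Kaplan-Meier applied to an outcome without death leaves no other option: counting the death as an event would change the outcome. The curve then treats patients who died as if they could still develop heart failure, and the incidence comes out too high.

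There is also a question of reading. Cardiac death is something the strategy is meant to reduce, and it also removes patients from the risk of heart failure. A comparison of heart failure alone therefore mixes two things: how often heart failure develops, and how many patients live long enough to develop it. Without deaths by arm next to it, neither a difference nor its absence can be interpreted with confidence.

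For the primary endpoint only non-cardiac death competes, so the same issue is weaker there.

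**Working it through.** **1. The plan's own figure.** Inputs from Sample Size Estimation: 1.03% and 2.6% per year, three years, two-sided alpha 0.05, power 0.80. I take the stated 1.03 as given. Three-year proportions are 3 × 1.03% = 3.09% and 3 × 2.6% = 7.8%; their mean is 5.445%.

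n = [1.96 × √(2 × 0.05445 × 0.94555) + 0.8416 × √(0.0309 × 0.9691 + 0.078 × 0.922)]² / (0.078 − 0.0309)² = (0.6289 + 0.2686)² / 0.04710² ≈ 363.1, rounded up to **364 per arm**, as stated. No part of this involves heart failure, so the point leaves it untouched.

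**2. Formulas for the overstatement.** With constant hazards h (event) and d (competing death) over T years:
- one minus Kaplan-Meier = 1 − exp(−hT)
- cumulative incidence = h/(h+d) × [1 − exp(−(h+d)T)]

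The article gives no heart-failure rate and no separate death rate, so h and d are assumptions and a range is shown.

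**3. Heart failure, h = 1% and d = 2% per year.**
- T = 3: 1 − exp(−0.03) = 2.955%; (0.01/0.03) × [1 − exp(−0.09)] = 2.869%. The gap is 0.086 percentage points, 3% in relative terms.
- T = 5.3, about the longest possible follow-up under Timing (September 2007 to December 2012): 5.162% against 4.900%. The gap is 0.26 points, 5% relative.

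**4. Range at 3 years.** Take heart failure at 0.5-3% per year and control cardiac death at 0.5-2.6% per year. The upper end is the plan's whole control event rate, as if every event were fatal. Screened-arm death is control × 1.03/2.6.
- Overstatement in the control arm: 0.01 to 0.32 points.
- Overstatement in the screened arm: 0.004 to 0.13 points.
- Middle case (heart failure 2%, control death 1%): Kaplan-Meier gives 5.82% in both arms; cumulative incidence gives 5.74% in control and 5.79% in screened.
- Severe case, all deaths at 4% per year: 2.955% against 2.786% when heart failure is 1% per year, and 8.607% against 8.118% when it is 3%, so up to 0.49 points.

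**5. Primary endpoint, h = 2.6% per year, non-cardiac death only.** Kaplan-Meier gives 7.504%. Cumulative incidence is 7.481% at d = 0.2% per year, 7.394% at 1% and 7.286% at 2%. The gap is 0.02, 0.11 and 0.22 points.

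**6. Comparison between arms, with no true effect on heart failure.**
- Independent hazards: the heart-failure hazard is equal in the two arms, so Kaplan-Meier, log-rank and cause-specific Cox compare like with like (ratio 1.00). The cumulative incidence ratio, screened to control, is 1.005 to 1.024 over the range in step 4, at most 0.7 extra cases per 364.
- Shared gamma frailty between heart failure and death (simulated): cause-specific rate ratio 1.00-1.02 at frailty variance 1, and 1.02-1.06 at the extreme variance 3.

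**The case against.** The strongest reply is that the Statistical analysis section is three sentences in a journal article. Handling of competing events normally belongs in the full protocol or the analysis plan, neither of which is shown, and the article never says that deaths are censored. That is fair as far as silence goes, and silence is not the point here. The article does choose an estimator of incidence, and for an outcome without death that choice implies censoring.

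Second, the primary analysis is sound. Cardiac death is a component, the remaining competition is slight (step 5), and Kaplan-Meier, log-rank and Cox are a standard choice. This stands in full.

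Third, the bias is small. The age limit below 70 and the exclusion of known heart failure and life-threatening conditions also keep competing mortality down. This stands too, and it sets the weight of the point.

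Fourth, a reader might infer from Participant enrolment that non-cardiac deaths will go unrecorded. The text does not support that. It says what will be notified and verified, not that nothing else is kept. Classifying a death as cardiac requires knowing of it, and every patient is to be contacted at the end. What remains is that date and cause of all deaths are not named explicitly, and the analysis needs them.

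**Conclusion.** The point holds as a minor one about the secondary outcome. One minus Kaplan-Meier overstates heart-failure incidence by about 0.1 percentage points at 3 years under assumed rates of 1% per year for heart failure and 2% for death. The gap is larger with longer follow-up or higher mortality (0.26 points at 5.3 years; 0.49 in the severe case of step 4). All of this rests on constant hazards and on rates the article does not give. Heart failure alone is also hard to interpret when screening is meant to change cardiac death. The primary analysis and the sample size stand.

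A reader might go further and infer that Kaplan-Meier would turn a real benefit on death into a marked excess of heart failure. For example, control cardiac death of 1% per year cut by 1.03/2.6 means about 6.5 deaths prevented per 364. If 30-50% of those survivors developed heart failure, that would add 1.9-3.2 cases to about 10.8, or 18-30%. The documents do not support this, for three reasons.
- The 30-50% has no source. With about 1.5 years of follow-up left on average, it implies a hazard of −ln(0.7)/1.5 = 24% to −ln(0.5)/1.5 = 46% per year, against the assumed 1%.
- Under independent hazards the planned tests show no excess, and under shared frailty only 1.00-1.06. An excess from lives saved is mainly a property of cumulative incidence, which would display it rather than remove it.
- The Secondary objective itself links heart failure to a preceding acute coronary syndrome, so effective screening should also lower heart failure. The net direction is unknown.

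**What to change.** In Statistical analysis:
- Estimate heart-failure incidence by the Aalen-Johansen cumulative incidence function, with death as the competing event.
- Keep log-rank and Cox for heart failure, described as cause-specific analyses.
- Report deaths by arm beside the heart-failure result.
- Add time to first heart failure or cardiac death as a supportive analysis, with components shown separately. It should not replace heart failure as the secondary outcome, because that would change the question.
- Optionally, add acute coronary syndrome or death from any cause as a sensitivity analysis of the primary endpoint; it has no competing death.

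In Participant enrolment, state that the date and cause of every death will be recorded in both arms.

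The cost is a few lines of text, standard software, two fields on the data form and a little more analysis work. The drawback is that the supportive composite shares cardiac death with the primary endpoint, so the two results are not independent evidence.

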### Interim Analyses

During the study interim analyses will be performed every year with the scope of verifying the correctness of the assumptions made for sample size estimation with regard to the primary end point event rate (this information can influence the duration of follow up) and to avoid unforecast excess of event rate in the treatment group.

### Economic evaluation

We will assess the incremental costs and the economic consequences of screening for asymptomatic coronary artery disease in diabetic patients with the aim of revascularization compared with usual care alone according to established methods for the analysis of patient-level data [25]. We will estimate all health care consumption and costs of both groups verifying hospital admissions from hospital records.

### Ethical consideration

The study will be conducted in accordance with European Commission guidelines for Good Clinical Practice and performed according to the revised Declaration of Helsinki. The study protocol was approved by local Ethical Committee.

The trial was registered at ClinicalTrial: the U.S. National Institute of Health registry of federally and privately supported clinical trials conducted in the United States and around the world [NCT00547872].

### Publication Policy

The study results will be submitted for publication in an appropriate journal irrespective of the outcome. Trial data will be reported according to the Consolidated Standards of Reporting Trials (CONSORT statements) [26]. The principal investigator will be responsible for timely generation of report manuscripts, and prior to submission the co-investigators will review and approve study results.

### Timing

September 2007 - Recruitment starts

December 2009 - Recruitment completed

December 2011 - Last participant completes 2-year follow-up

February 2012 - Analysis and publication of 2-year data

December 2012 - Last participant completes 3-year follow-up

February 2013 - Analysis of 3-year data and final publication

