### Sample Size Estimation

The sample size estimates are based on the following assumptions:

• *Follow up for three years*

• *Event rate in screened population: *1.03/year

Based on existing data we can assume that about 80% patients will test negative [20] and run a risk of 0.97% per year [21] while the remaining 20% of patients will test positive running a risk of 1.03% per year after treatment according to the results of the ACIP trial [22]. This results in a mean risk of 1.03 per year within the group.

• *Event rate in follow up population: *2.6/year

The cardiac event rate reported in over 10000 Italian diabetic patients without evidence of cardiac disease was collected by the Italian Istituto Superiore di Sanità (Diabetes and Informatics Study Group): the cumulative incidence of cardiac events was 2.88% per year in men and 2.33% per year in women [23].

• *Two-sided tests of significance at an alpha = 0.05*

• *Power analysis of 0.80*

Given these assumptions, the total number of subjects to be enrolled is of 364 patients for each arm [24].

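### Two published outcome analyses (2-year and 3-year) share one two-sided 0.05 that the sample size spends on the 3-year comparison, and follow-up may change after yearly looks not limited to pooled data

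*Protocol article*

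**What the plan says.** The Sample Size Estimation section of the protocol article lists "Follow up for three years", "Two-sided tests of significance at an alpha = 0.05" and "Power analysis of 0.80". It assumes 2.6% per year in the control arm. For the screened arm it states: "This results in a mean risk of 1.03 per year within the group". The result is 364 patients per arm.

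The Timing section gives two published analyses: "February 2012 - Analysis and publication of 2-year data" and "February 2013 - Analysis of 3-year data and final publication". Between them, in December 2012, the last participant reaches three years.

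The Interim Analyses section plans a look every year with two purposes. One is to check the sample-size assumptions about the primary event rate, with the remark that "this information can influence the duration of follow up". The other is to guard against an unexpected excess of events in the treatment group.

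The Statistical analysis section names a logrank comparison of Kaplan-Meier curves and Cox regression, by intention to treat. It gives no analysis time and does not say which of the two published analyses carries the claim. The Study Design section describes the trial as open-label.

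**The concern.** The trial is sized for one test at three years, yet the outcome data are to be analysed and published twice. If a significant result at either time could be presented as the trial's finding, the false-positive rate is no longer 0.05.

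The yearly looks raise a second question. The assumptions to be verified are 1.03 and 2.6 per year, one for each arm. Checking them literally means seeing the rates by arm, and the harm check needs by-arm data in any case. The same exercise may alter the length of follow-up. If that decision is made with the arm difference in view, the final test is no longer a fixed-design test.

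Third, publishing arm results before the last 3-year visit in an open-label trial tells the clinics that follow both arms how the arms compare. That could change how the remaining control patients are tested or referred.

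**Working it through.** **1. Reproduce 364 per arm.** Three-year risks, linear in time: p1 = 3 × 2.6% = 7.8% and p2 = 3 × 1.03% = 3.09%, so p̄ = 5.445%. With pooled variance and no continuity correction,

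n = [1.960 × √(2p̄(1−p̄)) + 0.8416 × √(p1(1−p1) + p2(1−p2))]² / (p1−p2)²
= [1.960 × 0.3209 + 0.8416 × 0.3192]² / 0.0471²
= 0.8056 / 0.002218 = 363.1, rounded up to **364**.

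Power at 364 is 0.801. The figure matches exactly, so the full two-sided 0.05 goes to the 3-year comparison and none is reserved for an earlier one. (The components given for the screened arm average 0.8 × 0.97 + 0.2 × 1.03 = 0.98, not 1.03. That is a separate matter; I use the stated 1.03 because it is what yields 364.)

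**2. Power of a 2-year test.** Risks are 2 × 2.6% = 5.2% and 2 × 1.03% = 2.06%, with 364 per arm:

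Φ[(0.0314 × √364 − 1.960 × 0.2645) / 0.2636] = Φ(0.306) = **0.62**.

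**3. Type I error if both analyses are tested at 0.05.** With information fraction t at the first analysis, Z1 and Z2 are bivariate normal with correlation √t, and the error is 1 − P(|Z1| ≤ 1.96 and |Z2| ≤ 1.96).

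| Basis for t (assumed) | t | Two-sided error |
|---|---|---|
| Each patient's first 2 years against 3 years | 0.67 | 0.077 |
| Calendar cut-offs, follow-up not capped at 3 years | 0.76 | 0.073 |
| Calendar cut-offs, follow-up capped at 3 years | 0.92 to 0.93 | 0.063 to 0.062 |

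The capped fraction follows from uniform accrual over the 28 months from September 2007 to December 2009. At a cut at the end of December 2011 (month 52), a patient entered at month u > 16 still owes u − 16 months. The mean is 12² / (2 × 28) = 2.57 months, which is 7.1% of 36, so t = 0.93. A cut at the start of that month gives 13² / 56 = 3.02 months, or 8.4%, so t = 0.92.

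**4. Follow-up left when the 2-year results appear.** At the end of February 2012 (month 54), patients entered after month 18 still owe u − 18 months. The mean is 10² / 56 = 1.79 months, or **5.0%** of 3-year person-time. By then 18/28 = 64% of patients have completed three years.

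**5. What a split of alpha would cost.** O'Brien-Fleming-type spending at t = 2/3 gives a first level of 2[1 − Φ(1.96/√0.667)] = 0.016 and a final level of about 0.044. At 0.044 the formula in step 1 needs 378 per arm, and power at 364 is 0.785. Equal levels of about 0.032 need 413 per arm, with power 0.745 at 364.

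**6. Information at the early yearly looks.** The pooled rate is (1.03 + 2.6)/2 = 1.815% per year. After 12 months, 728 × 12/28 = 312 patients with a mean of 0.5 years give 312 × 0.5 × 0.01815 = 2.8 events. After 24 months, 624 patients with a mean of 1 year give about 11.

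**The case against.** The strongest reply is that the article never says the 2-year data are tested at 0.05. The 0.05 appears only as a sample-size input, next to three years of follow-up, and only the 2013 output is called final. On that reading the 3-year comparison is the one test, and its error is 0.05. This stands, and it makes the inflation in step 3 conditional. That the 2-year analysis compares the arms is itself an inference, though a reasonable one, since a between-arm comparison is the only outcome analysis described.

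A reader might infer that each yearly look is a further efficacy test at 0.05, or that follow-up will be extended whenever the 3-year result misses significance. The text supports neither. The looks are described as an event-rate check and a harm check, and no extension rule is given. A check on pooled counts does not materially inflate type I error, and a harm-only look does not raise the chance of a false claim of benefit.

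The errors in step 3 are also two-sided. On the benefit side alone they are about half, 3.1% to 3.8% against 2.5%.

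A reader might further infer that early publication spoils the whole third year of the control arm. Staggered entry rules that out: about 5% of person-time remains under uniform accrual. Under intention to treat, late testing of controls would tend to dilute an effect rather than create one.

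Finally, boundaries and adaptation rules often sit in a full protocol or analysis plan, which is not shown here, so their absence is not the point. What remains is what the article itself fixes: two published analyses, an alpha sized for one of them, and a follow-up length open to change after looks at arm-specific assumptions.

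**Conclusion.** The point holds in conditional form. If either published analysis may support a claim at 0.05, the overall two-sided error is about 6.2% to 7.7%. The information fraction of 0.93 to 0.67 behind that range is an assumption, as is uniform accrual. If the 3-year analysis is the only confirmatory test and follow-up is not altered in the light of arm results, the error stays at 0.05.

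Changing follow-up after seeing by-arm results could add inflation. I put no figure on it because the article gives no rule to evaluate. Contamination of the control arm is possible but small. The 2-year comparison is also a weak basis for a claim at 62% power. The documents do not support saying outright that the type I error exceeds 0.05.

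**What to change.** - Name the February 2013 analysis of 3-year data as the only confirmatory efficacy test, at two-sided 0.05, and hold the 2-year arm comparison until then. The 364 per arm is unchanged; the cost is one publication delayed by a year.
- If the arm comparison must appear in 2012, split alpha: about 0.016 at two years and 0.044 at the end, for an information fraction of two-thirds. Power at 364 per arm falls from 0.801 to about 0.785. The levels must be recomputed if the actual fraction differs.
- Base any change in follow-up on the pooled primary event count only, by a rule fixed in advance. The first two yearly looks, with about 3 and 11 expected events, are too thin to support such a change.
- State that by-arm interim looks serve the harm check only and play no part in decisions on follow-up length or efficacy.

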## Discussion

The study will be among the first randomised trials to investigate the effectiveness and cost-utility of a strategy of screening for unknown coronary artery disease in diabetic patients aimed at revascularisation. Recently the publication of DIAD trial results [27] demonstrates that screening asymptomatic diabetic patients by myocardial perfusion imaging without any treatment strategy does not affect outcome. This study cannot be considered the last word in this field because a screening plan should be performed only if treatment is available when positive cases are found. DIAD study design is not thought to test screening and treatment together but screening alone. Moreover the screening tool was myocardial perfusion imaging, a very sensitive and specific test, but with considerable radiation burden. In case of favourable results such a strategy would not be applicable to a large population due to costs and risks. Exercise tolerance testing is a simple and cheap test with low or no risk, it does not deliver radiations. In case of positive results the same strategy would be completely feasible in the *real world*.

Even the publication of BARI 2D [28] trial results does not represent the final answer to the dispute. BARI 2D was not designed as screening trial, patients with left main disease were excluded and patients with history of heart failure or ischemic heart disease were included. Furthermore a benefit in terms of major cardiovascular events was observed in patients undergone coronary artery bypass.

This study is designed as screening and treatment study and mandate coronary angiography for every patient with positive exercise testing. In case of coronary blockages, revascularization (percutaneous or surgical) is proposed. The results will help to establish if a screening strategy followed by revascularization is the best approach to high risk diabetic patients.
